### Sample size estimation

G*Power was used to determine the sample size. Based on the previous intervention studies, the most frequently reported effect size was ranged from moderate (0.25) to high (0.70) [28, 29], a moderate effect size of 0.25 will be adopted for the current study. To ensure a power of 80% probability for detecting a treatment difference at a two-sided 5% level of significance, a sample size of 35 participants per group (total 105 for 3 groups) is expected to recruit. Yet, considering a 20% of potential dropout rate, a sample size of 42 participants per group (total 126 for 3 groups) will be required in the current study for the two-way repeated measures in three-time points. It is decided a total of 126 participants will be recruited. In order to satisfy the culture of KSA that males and females should undergo walking intervention separately in the group, an equal number of males and females (63 M and 63 F) will be recruited and randomly and equally assigned to the two intervention groups and control group. Moreover, in order to have an approximate mean age in each intervention group, the participants will be divided into 2 groups (60–64 and 65 to 70) for the randomization.

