### Statistical analysis

Descriptive statistics will be used to describe baseline characteristics such as gender, age, living status (alone or with family), body height, body weight, resting heart rate, and blood pressure of the participants in the study. The primary outcomes will be analyzed using an intention-to-treat (ITT) approach, and a sensitivity test will subsequently be conducted using the available data. Missing data will be replaced using the last observation carried forward method. For the secondary outcomes, a per-protocol analysis will be conducted using the available data. The statistical significance level was set at *p* < .05. All data will be analyzed using SPSS Version 26.0 (IBM, Chicago, IL). For the within-group test, a one-way repeated measure analysis of variance (ANOVA) will be applied to each group to determine the changes of each outcome parameter among the three-time points (i.e., pretest, posttest, and follow-up test). When the sphericity assumption was violated, the Greenhouse– Geisser correction will be used when epsilon < 0.75, or the Huynh–Feldt correction will be used when epsilon > 0.75. Post hoc analysis with Bonferroni correction will be conducted to explore the differences between the pretest and posttest, as well as posttest and follow-up test. The mean differences with 95% confidence intervals (CIs) will be reported. For the inter-group test, a one-way analysis of covariance (ANCOVA) with the baseline value as a covariate will be conducted at the posttest, and follow-up test to determine the group effect on each outcome parameter. Subsequently, the differences between the intervention groups and the control group will be analyzed through planned contrasts.

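### The between-group ANCOVA omits sex and age group, the factors used to balance the randomisation; if they stay prognostic after baseline, its tests are mildly conservative

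*Protocol article*

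**What the plan says.** All references are to the protocol article.

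- **Sex.** Sample size estimation plans that "an equal number of males and females (63 M and 63 F) will be recruited and randomly and equally assigned"; this split covers all three arms. Grouping and randomization repeats the 63 men and 63 women. The intervention and control group sections give 21 men and 21 women per arm.
- **Age group.** Under Sample size estimation, "the participants will be divided into 2 groups (60–64 and 65 to 70) for the randomization". The stated aim is a similar mean age across the groups. Grouping and randomization describes a draw of lots for men and women and does not mention age.
- **Analysis.** Under Statistical analysis, the inter-group test is "a one-way analysis of covariance (ANCOVA) with the baseline value as a covariate", applied at posttest and at follow-up to each outcome, followed by planned contrasts of the intervention groups with control. One-way means that group is the only factor. Sex and age appear in that section only as descriptive baseline characteristics.

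**The concern.** Forcing the arms to be alike on a factor removes that factor's contribution to the sampling variation of the arm difference. A model without the factor still leaves its variation in the residual. If the factor predicts the outcome given baseline, the model-based standard error then exceeds the true one, confidence intervals are wider than necessary, and the test rejects less often than its nominal level. The design has arranged for extra precision that the analysis does not collect.

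This affects the between-group results for all three primary outcomes (quality of life, physical performance, cognition) and for the secondary outcomes analysed with the same model.

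**Working it through.** **Inputs from the article (Sample size estimation):** "at a two-sided 5% level of significance"; "To ensure a power of 80% probability"; "a moderate effect size of 0.25 will be adopted for the current study", read here as Cohen's f; 35 per group (105 in total) before dropout; 42 per group (126 in total) recruited.

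**Inputs assumed, because the article gives none:** the correlation r between baseline and later value (0.6, with 0.5 and 0.7 as alternatives), and q, the share of the residual variance after baseline that sex and age group explain (0–10%). The range starts at zero because baseline already absorbs much of any sex or age effect.

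**Step 1: the plan's own figure.** For the between-groups test of a repeated-measures ANOVA with m = 3 time points and an assumed correlation of 0.5 among them, the noncentrality is λ = f²·N·m / (1 + (m−1)·0.5). At N = 105 this is 0.0625 × 105 × 3 / 2 = 9.84, and power is 79.7%. The exact search gives 108, so the stated 105 reproduces within 3%. The 42 per group is 35 × 1.2. The calculation contains no allowance for a gain from stratification.

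**Step 2: what omission does to the ANCOVA.**

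- Overstatement of the standard error: 1/√(1−q).
- Actual type I error of the three-arm F test without the factors: P(F(2, 101) > 3.086/(1−q)), where 101 = 105 − 4.
- Noncentrality: λ = N·f² / [(1−r²)(1−q)]. At q = 0 and r = 0.6 this is 105 × 0.0625 / 0.64 = 10.25.
- Power without the factors: noncentral F(2, 101), critical value 3.086/(1−q). Power with them: noncentral F(2, 99), usual critical value.

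Results for N = 105, r = 0.6:

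| q | SE overstated by | Actual type I error, factors omitted | Power, factors omitted | Power, factors included |
|---|---|---|---|---|
| 0% | 0% | 5.0% | 81.3% | 81.3% |
| 2% | 1.0% | 4.7% | 81.5% | 82.1% |
| 5% | 2.6% | 4.3% | 81.7% | 83.4% |
| 10% | 5.4% | 3.6% | 82.1% | 85.4% |

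The gain forgone at q = 10% depends on r: 74.9% against 79.1% at r = 0.5, and 90.4% against 92.6% at r = 0.7. That is about 4 and 2 points, against about 3 at r = 0.6.

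For a single two-arm contrast with a t reference on 101 degrees of freedom, the actual error is 2·P(t > 1.984/√(1−q)): 4.4% at q = 5% and 3.9% at q = 10%, slightly nearer to 5% than for the three-arm test.

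**Step 3: simulation check.** Stratified allocation, 42 per arm, r = 0.6, true difference 0.5 SD, 6,000 runs, two-arm contrast:

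| q | Mean model SE, factors omitted | Empirical SD of the estimate | Power, factors omitted | Power, factors included |
|---|---|---|---|---|
| 0% | 0.175 | 0.177 | 80.7% | 80.7% |
| 5% | 0.175 | 0.170 | 80.8% | 82.4% |
| 10% | 0.175 | 0.169 | 81.1% | 84.2% |

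With no true difference, the model without the factors rejected in 5.2%, 4.1% and 3.9% of runs. Direction and size agree with Step 2.

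**The case against.** The strongest case against the point is that its consequence is conditional and small. Every between-group model already carries the outcome's own baseline. Participants are healthy, live independently, have no diagnosed cognitive impairment and span only ages 60–70, so sex and age group may add little. At q = 0–2% the loss is 0–0.6 power points and 0–1% in the standard error. This stands, and it sets the size of the point. It does not remove the mismatch: the article states the model in full, so this is not a detail left to an unseen analysis plan.

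A reader might infer more than the documents support:

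- **That the standard errors are certainly too large and planned power is lost.** Outcomes that vary with sex and age need not do so given baseline, and the article has no figure on this. Omitting the factors never takes power below its value at q = 0; only a possible gain is forgone. Whether the ANCOVA reaches 80% at all depends on the baseline correlation, not on this omission.
- **That the result is biased, falsely positive, or under-sized.** The estimate is not biased, the type I error falls rather than rises, and the sample size calculation assumed no stratification gain.
- **That sex must be in the model because men and women have different trainers.** Qualified trainers serve only the supervised arm. Research assistants attend the individual arm, and the control arm has no sessions. A trainer effect tied to sex within one arm is a sex-by-arm difference, which a sex main effect does not capture.
- **That age balance is as firm as sex balance.** It rests on one sentence under Sample size estimation, with no numbers per age band. Grouping and randomization names sex only. Exclusions for low attendance or changed lifestyle, where applied, may also disturb the balance in the analysed set; the figures above ignore this.

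**Conclusion.** The point holds in conditional form. The design balances on sex and, by one of its two descriptions, on age group, while the stated between-group model contains neither. If they explain 0–10% of the residual variance after baseline, standard errors are overstated by 0–5%, the three-arm test runs at about 5.0–3.6% instead of 5%, and 0 to about 3 power points are forgone (about 2 to 4 at the upper end for baseline correlations of 0.7 to 0.5). Both q and the correlation are assumptions. The mismatch itself is certain; its practical effect is probably small and errs on the conservative side.

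The change is still worth making. At q = 0 adjustment costs no measurable power (81.3% either way), and covariates added after the data are seen would invite doubt about how they were chosen.

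**What to change.** In Statistical analysis, state that every between-group ANCOVA, at posttest and at follow-up, includes sex and age group (60–64, 65–70) as fixed factors next to the baseline value, and that the planned contrasts come from that model. Make the change before the data are unblinded. It costs one sentence and two error degrees of freedom (101 to 99 at 105 analysed); no new data are needed, because sex and age are already recorded.

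Reconcile Grouping and randomization with Sample size estimation on whether the draw of lots is carried out within age groups as well as by sex, so that the factors in the model are those used in the allocation.

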#### Discussion and conclusion

The purpose of the proposed study is to compare the effects of supervised group-based walking and non-supervised individual-based walking interventions on frailty, cognitive function and quality of life among inactive older adults in Saudi Arabia. We are aware that walking related research in Saudi Arabia has tended to be cross-sectional and environment based. Using questionnaire surveys and GIS applications, environmental researchers determined that 80% of participants expressed a liking for walking due to the average accessibility of walking routes. Additionally, the study revealed that improving sidewalk walkability should also increase pedestrian behavior. However, as Saudi Arabia is in arid regions, the hot weather could have decreased the motivation to walk. Therefore, it could be considered as a potential issue in the current study [20, 21]. Additionally, researchers found that older adults with chronic disease in Saudi Arabia spent less time on walking-related activities, for which more attention was required. While physical therapists have also used walking-related therapeutic techniques with stroke patients [35, 36]. Nevertheless, the findings of this study will not only help identify the difference in effects caused by supervised group-based walking and non-supervised individual-based walking interventions, but they will also create awareness in Saudi Arabia among government and the general public about the ageing problem and ways to improve intervention outcomes. With the evidence, the government, universities, and the related non-governmental organizations in Saudi Arabia will have strong justifications for formulating guidelines and policies, and more importantly allocating more resources to promoting healthy and active ageing in their country.

## Data Availability

Not Applicable.

## Abbreviations

WHO: World Health Organization
KSA: Kingdom of Saudi Arabia
PACES: Physical Activity Enjoyment Scale
HRQoL: Health-related quality of life
PPT: Physical Performance Test
MMSE: The Mini-mental state examination
ANOVA: One-way repeated measure analysis of variance
ANCOVA: One-way analysis of covariance
